#### 5.4. - EXCLUSION CRITERIA

Exclusion criteria are the following:

- Missing informed consent form
- Current clinically manifested infection or within the last two weeks
- Current CRP-value > 50mg/L or within the last two weeks
- Intake of any medication applied for immunosuppressive purposes
- Pregnancy or lactation
- Participation in a different interventional study

#### 5.5. RECRUITMENT AND SAMPLE SIZE

Recruitment for the study will start after Ethics Committee and competent authorities' approval. After checking inclusion and exclusion criteria, the patient will receive the patient information form. Patients will be considered enrolled in the study when the informed consent has been signed.

During a previously conducted clinical study (Perci study, unpublished) with ESRD patients we experienced a 20% drop out rate by a study length of four months. Due to the prolonged study length of total 6 months, we expect a drop out rate of 30% for this study.

Therefore a total of 50 patients, including a 30% drop out rate, are to be included in the study.

- Ø 25 patients will be randomized to the treatment group starting with MCO treatment
- Ø 25 patients will be randomized to the treatment group starting with HF treatment

#### 5.6 PATIENT WITHDRAWAL AND REPLACEMENT

Patients are free to withdraw from the study at any time without having to justify their decision. When a patient decides to withdraw from a study, he/she will be systematically contacted and given the opportunity to provide information about the reason(s) of his/her withdrawal and possible occurrence of an adverse event.

If at anytime the investigator considers that malfunctions/AEs could possibly lead to a deficiency in the patient's treatment, the treatment in question shall be discontinued and replaced by a standard treatment.

Patients may be withdrawn from the study at any time and at the investigator's discretion.

Patients must be withdrawn from the study if any of the following occurs:

- Any event which, in the opinion of the investigator, may either endanger the health of the patient, or may incorrectly influence the result of the study
- Patients refusing or not considered capable, as judged by the investigator, of following instructions of the study.

If a patient be withdrawn from the study, the Investigator has to inform the Study Manager in the shortest possible time, irrespective of the reason for withdrawal. Reason for withdrawal should be recorded in the Case Report Form (CRF).

If withdrawal is related to the possible occurrence of adverse events, the patient will be followed up according to the adverse event procedure.

Withdrawn patients will not be replaced as a drop out rate of 30% is included in the patient size evaluation.

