## 7. LABORATORY AND ASSESSMENT

Blood pressure will be determined according to routine procedure.

Blood sampling will be done as described in the sampling schedule. Central Laboratory analyses are summarized in Table 2 in the section Central analyzes. Further blood samples are drawn for exploratory analysis:

- Explorative Proteomic analysis at NMI Reutlingen, Germany
- Explorative analysis of AGE's at Food Chemistry Laboratory Halle, Germany
- Explorative analysis at Charité Berlin, Germany
- Explorative analysis at University Clinic Halle, Germany
- Explorative analysis at Gambro laboratories Hechingen, Germany
- Explorative analysis of  $\mu$ RNA at Internal Medicine Department of Homburg University, Germany

The labelling of laboratory samples must ensure that the laboratory assessments are executed in a blinded fashion by the laboratory personal.

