#### 10.3. BLINDING

Not applicable (open label study)

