#### Primary analysis population:

The primary analysis population will be the modified ITT population. Patients with clinical events making the analysis of the primary endpoint impossible will be excluded after a blind data review. The remaining drop outs will be included in the analysis if results are available for at least one treatment phase.

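### Section 5.6 obliges unblinded investigators to withdraw patients for events they think may distort the result, and provides no endpoint sampling afterwards

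*Protocol*

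**What the plan says.** Section 5.6 introduces its compulsory grounds with "Patients must be withdrawn from the study if any of the following occurs". The first ground has two limbs, both resting on the investigator's opinion: an event may endanger the patient's health, "or may incorrectly influence the result of the study". The section does not list events of the second kind and asks for no blinded or independent decision. Just before this it adds a general power: "Patients may be withdrawn from the study at any time and at the investigator's discretion". The reason for withdrawal goes into the CRF and the Study Manager is told promptly. Follow-up is described only for withdrawals related to adverse events, under the adverse event procedure. On numbers it says: "Withdrawn patients will not be replaced as a drop out rate of 30% is included in the patient size evaluation".

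Section 10.3 on blinding reads "Not applicable (open label study". Section 7 requires sample labelling such that "laboratory assessments are executed in a blinded fashion by the laboratory personal".

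Section 17.4 states: "The primary analysis population will be the modified ITT population". Drop-outs stay in it if one treatment phase has results. Patients whose clinical events make the primary endpoint impossible to analyse are removed in a blind data review. For that review treatment arm is masked, primary endpoint data are deleted, and each principal investigator sees only the other site's patients.

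**The concern.** Whether an event influences the result incorrectly is a judgement about the outcome, and here it is made at the bedside with the membrane known. The primary endpoint is TNF-alpha mRNA in PBMC, taken as a measure of inflammation. The protocol's own list of expected events (section 12.3.4) includes exit site infection, septicaemia and endocarditis, and section 5.4 excludes recent infection and high CRP at entry. So the events most likely to be judged distorting are close to the endpoint, and some could depend on the membrane.

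If patients are withdrawn for such events more readily under one membrane, or if the events are commoner under one membrane, the observed values no longer represent the randomized patients. Ordinary GEE is not generally valid when missingness depends on unobserved outcomes.

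The rule also cuts across the protocol's own safeguard. Section 17.4 reserves exclusions for a blinded group with a strict threshold (analysis impossible). Section 5.6 lets an unblinded investigator act earlier, on the site's own patients, with a looser threshold (may influence).

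**Working it through.** **1. The plan's figures.** Inputs from section 17.1.1: effect size 0.5 in intraindividual SD units, two-sided 0.05, power 80%, 30% drop-out. A paired t-test (noncentral t, noncentrality 0.5 × √n) gives power 0.795 at n = 33 and 0.808 at n = 34, so 34 evaluable patients is reproduced. 50 × 0.70 = 35 evaluable, as stated. The sample size is not the problem.

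**2. What each withdrawal time costs.** Sampling times are from section 7.3; the primary comparison uses T1/T3 and T4/T6.

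| Withdrawn | Primary endpoint data held | Place in the primary analysis |
|---|---|---|
| Before T3 (session 13) | T1 at most | No 4-week result |
| After T3, before T4 (session 25) | T1, T3 | One phase, no within-patient contrast |
| After T4, before T6 (session 37) | T1, T3, T4 | One phase result, no within-patient contrast |
| After T6, before T7 (session 61) | T1, T3, T4, T6 | Complete; only exploratory Phase 3 is lost |

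**3. What the safeguards reach.** Laboratory blinding protects samples already taken. The blind review governs which collected data are analysed. The modified ITT rule keeps a phase already completed. None governs the decision that ends sampling.

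**4. Illustration of size.** The documents give no rate of such withdrawals and no link to the outcome, so both are assumed. The check used 50 patients, no true treatment effect and a within-patient correlation of 0.5. The SD of the difference is then √(2 × (1 − 0.5)) = 1, the unit of the planned 0.5. Of the 50, s are withdrawn during the MCO phase on a cue correlated r with the MCO value. One-phase patients are kept, and a GEE with treatment and period is fitted (1,500 runs; no baseline or centre terms, no other drop-out).

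| s | r | Mean bias (SD) | Two-sided type I error |
|---|---|---|---|
| 0 | – | +0.009 | 0.062 |
| 5 | 0.3 | −0.038 | 0.075 |
| 5 | 0.5 | −0.058 | 0.071 |
| 5 | 0.7 | −0.089 | 0.113 |
| 8 | 0.5 | −0.094 | 0.117 |

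Simulation error matters. For 0.071 against 0.062 the standard error of the difference is √(0.071 × 0.929/1500 + 0.062 × 0.938/1500) ≈ 0.009, so that contrast is within noise. For 0.117 against 0.062 it is about 0.010, so that one is not. With no withdrawals the true bias is zero, so the +0.009 in the first row is itself noise.

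A complete-pairs version (15 of 50 lost, s = 5 of them selective, 20,000 runs) gave biases of −0.057, −0.095 and −0.131 and type I errors of 0.066, 0.092 and 0.134 at r = 0.3, 0.5 and 0.7. With no correlation the error stayed between 0.048 and 0.052. In that version the cue is correlated with the MCO-minus-HF difference. In the GEE version r = 0.5 with the MCO value is only 0.5 × (1 − 0.5)/1 = 0.25 with the difference. The two sets therefore cannot be subtracted to show how much the modified ITT rule helps.

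**The case against.** A reader might infer that investigators can drop patients with unwelcome TNF-alpha values. The text does not support that. The trigger is an event; the mRNA is measured centrally by blinded staff; and although the protocol does not say that results are withheld from sites, nothing says sites receive them during the study. The realistic route is clinical events judged with the membrane known.

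A reader might also infer that withdrawn patients vanish from the primary analysis. They do not: only those without a first phase result do. The blind review prevents selective exclusion later, and recording reasons for withdrawal makes the pattern visible. All of this stands, and it narrows the problem to samples that are never drawn.

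A third tempting reading is that the rule uses up a margin of one patient (35 against 34). Nothing shows that these withdrawals fall outside the 30% allowance, which was raised from 20% in the earlier study, and 79.5% against 80% power is negligible anyway.

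Finally, section 5.6 already describes replacing a study treatment with standard treatment apart from withdrawal, and deleting one phrase leaves the general discretion sentence in force. Both are fair points. The first shows that the separation exists in part and lacks only continued sampling; the second means that continued sampling must cover every investigator-initiated withdrawal.

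**Conclusion.** The point holds as a design defect in section 5.6: a mandatory, subjective, result-related ground for withdrawal, applied by investigators who know the membrane, with no endpoint sampling afterwards. Followed as written, it can produce informative loss that the existing safeguards limit but cannot undo.

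Its size cannot be derived from the documents. In the GEE illustration, five selective losses, all against MCO, move the estimate by about 0.04 to 0.09 SD, or 8% to 18% of the planned 0.5 (0.038/0.5 and 0.089/0.5). Clear inflation of the type I error needs either a strong link to the outcome (r = 0.7) or eight such losses. These are assumptions about behaviour and not predictions, and the direction could be reversed. No power shortfall is claimed. The change is worth making because it is cheap and because no analysis can recover the missing samples.

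**What to change.** In section 5.6:

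- Delete "or may incorrectly influence the result of the study" as a ground for withdrawal. Leave the patient-health ground exactly as it is; no clinical rule changes.
- State that ending the study dialyser, for any reason including investigator discretion, is separate from ending participation. Patients who consent keep giving the scheduled T3, T4, T6 and T7 samples.
- Record events thought to distort the endpoint in the CRF, with date and membrane in use. Leave any exclusion to the blind data review in section 17.4, and examine the effect of these events in a sensitivity analysis.

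The cost is a short protocol amendment. Section 7.3 already schedules these samples, draws them from the dialysis circuit without an extra puncture, and counts them in the 493 mL total. The downside is a few noisier values, some taken after the assigned dialyser was stopped, which should be flagged in the data.

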## 6. PATIENT TREATMENT

### 6.1. RECOMMENDATION FOR STUDY PRODUCTS IMPLEMENTATION

The procedure for product implementation is described in the Instructions For Use, available in the Investigator's Brochure (IB). All recommendations and warnings mentioned in these instructions shall be strictly taken into account.

Anytime the investigator considers that reported AEs could possibly lead to a deficiency in the patient's treatment.

### 6.2. CONCOMITANT MEDICATION

Any medication or treatment required for the welfare and health of the patients enrolled in the study will be administered at the investigator's discretion. All such concomitant medication shall be reported on the CRF and this, as soon as start of run in phase up to study end.

#### 6.2.1. Medication allowed

Any medication commonly prescribed for ESRD patients

#### 6.2.2. Medication not allowed

Any medication applied for immunosuppressive purposes.

### 6.3. TREATMENT DETAILS

#### 6.3.1. Dialysis treatment

Standard HD care three times per week

#### 6.3.2. Heparin strategy

The type of anticoagulation, the dosage, and the administration during HD sessions must be continued as individually prescribed during the study period and must be noted in the CRF.

### 6.4. PATIENT MEDICAL CARE AFTER CLINICAL STUDY CLOSURE

After the clinical investigation has been completed patients continuing renal replacement therapy and general medical care will be provided for the subjects

## 7. LABORATORY AND ASSESSMENT

Blood pressure will be determined according to routine procedure.

Blood sampling will be done as described in the sampling schedule. Central Laboratory analyses are summarized in Table 2 in the section Central analyzes. Further blood samples are drawn for exploratory analysis:

- Explorative Proteomic analysis at NMI Reutlingen, Germany
- Explorative analysis of AGE's at Food Chemistry Laboratory Halle, Germany
- Explorative analysis at Charité Berlin, Germany
- Explorative analysis at University Clinic Halle, Germany
- Explorative analysis at Gambro laboratories Hechingen, Germany
- Explorative analysis of  $\mu$ RNA at Internal Medicine Department of Homburg University, Germany

The labelling of laboratory samples must ensure that the laboratory assessments are executed in a blinded fashion by the laboratory personal.

### 7.1. STUDY VISITS

Seven Study visits will be done (Visit 1-7)

- Ø Visit 1 Screening and Inclusion visit (within two weeks prior start of “run in phase”)
- Ø Visit 2 (start “run in phase”): week 1; dialysis session -12 (week -4)
- Ø Visit 3 (start Phase 1, week 1; dialysis session 1):
- Ø Visit 4 (start Wash-out period: week 5; dialysis session 13)
- Ø Visit 5 (start Phase 2: week 9; dialysis session 25)
- Ø Visit 6 (start phase 3, week 13; dialysis session 37)
- Ø Visit 7 (end Phase 3: week 21; dialysis session 61)

### 7.2. SAMPLING SCHEDULE

There are three efficacy and safety periods, each period lasting at the most for eight weeks. During each week three HD treatments shall be performed.

### 7.3. SAMPLING DETAILS

#### 8 sampling time points

T0 pre dialysis session HD -12  
T1 pre dialysis session HD 1  
T2 post dialysis session HD1  
T3 pre dialysis session HD13  
T4 pre dialysis session HD 25  
T5 post dialysis session HD25  
T6 pre dialysis session HD 37  
T7 pre dialysis session HD 61

- Kinetics: 10 patients x 2 time points / à 6mL = 120mL

In 10 selected patients kinetic monitoring of inflammatory proteins will be done at 2 time points in the study (first treatment with MCO, first treatment with Revaclear). For this monitoring, an additional total of 6ml blood per time point will be drawn.

- Routine lab: 6 sampling à 5mL = 30mL
- 7 sampling exploratory lab à 15mL = 105ml (Charité)
- 7 sampling exploratory lab à 10mL = 70ml à 14,2 / 5,5mL = 82ml (Halle)
- 7 sampling exploratory lab à 5mL = 35ml (Halle Lebensmittelchemie)
- 7 sampling exploratory lab à 15mL = 105ml (Gambro)
- 7 sampling exploratory lab à 3mL = 21ml (NMI)
- 7 sampling exploratory lab à 1mL = 7 ml (Homburg University)

-----  
Total blood volume / per patient **493 mL**

- Ø Blood samples: No additional puncturing of the patient is necessary as the sampling will be performed from the extracorporeal circuit's arterial access needle.

In total a maximum of 493 mL blood volume will be collected during the entire study (6 month).

#### 7.4. PARAMETERS AND LABORATORY ANALYZES

In order to prevent any variation between tests, guidelines will be followed.

##### 7.4.1. Local analyzes

Locally analyzed samples will be performed according to local routine. Methods, units and ranges for the primary and secondary endpoint parameters shall be available to sponsor before study start.

##### 7.4.2. Central analyzes

Parameters and the methodology for centrally analyzed study parameters are presented in *Table 2*. Sampling, handling and storage details will be describe in more details during training at study site.

Table 2

| Centrally analyzed parameters - by [name] lab (Halle)       |                     |      |                     |                    |
|----------------------------------------------------------------|---------------------|------|---------------------|--------------------|
| Parameter / Method                                             | Quantitative rt-PCR | FACS |                     |                    |
| mRNA TNFa                                                      | x                   |      |                     |                    |
| mRNA IL-6                                                      | x                   |      |                     |                    |
| mRNA sTNFR1                                                    | x                   |      |                     |                    |
| mRNA sTNFR2                                                    | x                   |      |                     |                    |
| mRNA sVCAM                                                     | x                   |      |                     |                    |
| mRNA sIL-2R                                                    | x                   |      |                     |                    |
| mRNA Adiponectin                                               | x                   |      |                     |                    |
| Monocyte CD14/CD16 subpopulations                              |                     | x    |                     |                    |
| M-DC8 positive monocytes                                       |                     | x    |                     |                    |
| Centrally analyzed parameters - by Gambro Hechingen ([name]) |                     |      |                     |                    |
| Parameter / Method                                             | Elisa               | HPLC | Nephelometric Assay | Fluorometric Assay |
| Oxidized Albumin                                               |                     | x    |                     |                    |
| Albumin-gebundene Toxine                                       |                     | x    |                     |                    |
| Beta 2-microglobulin                                           |                     |      | x                   |                    |
| Myoglobin                                                      |                     |      | x                   |                    |
| Free Light Chain, kappa (κ-FLC)                                |                     |      | x                   |                    |
| Free Light Chain, lambda (λ-FLC)                               |                     |      | x                   |                    |
| α1-Microglobulin                                               |                     |      | x                   |                    |
| suPAR                                                          | x                   |      |                     |                    |
| beta Trace protein                                             |                     |      | x                   |                    |
| Pentraxin 3 (long) (PTX-3)                                     | x                   |      |                     |                    |
| Complement Factor D                                            | x                   |      |                     |                    |
| Glutathion oxidized*                                           | x                   |      |                     |                    |
| GSH/ GSSG Ratio *                                              |                     |      |                     | x                  |
| Fetuin A*                                                      | x                   |      |                     |                    |
| MGP*                                                           | x                   |      |                     |                    |
| Prolactin*                                                     | x                   |      |                     |                    |
| YKL-40*                                                        | x                   |      |                     |                    |
| Locally analyzed parameters in Charité and Halle               |                     |      |                     |                    |
| Routine laboratory Charité                                     |                     |      |                     |                    |
| Routine laboratory Halle                                       |                     |      |                     |                    |
| Locally analyzed parameters at NMI                             |                     |      |                     |                    |

| Parameter                 | Plex 1 | Plex 2 | Plex 3 | Plex 4 |
|---------------------------|--------|--------|--------|--------|
| ESelectin                 | X      |        |        |        |
| IL6sR                     | X      |        |        |        |
| MIF                       | X      |        |        |        |
| PLA2G7                    | X      |        |        |        |
| Rantes                    | X      |        |        |        |
| sFas                      | X      |        |        |        |
| sgp130                    | X      |        |        |        |
| sICAM                     | X      |        |        |        |
| sRAGE                     | X      |        |        |        |
| sTNFR1                    | X      |        |        |        |
| sTNFR2                    | X      |        |        |        |
| sVCAM                     | X      |        |        |        |
| GMCSF                     |        | X      |        |        |
| GRO                       |        | X      |        |        |
| IFNg                      |        | X      |        |        |
| IL10                      |        | X      |        |        |
| IL12p40                   |        | X      |        |        |
| IL12p70                   |        | X      |        |        |
| IL17A                     |        | X      |        |        |
| IL1b                      |        | X      |        |        |
| IL1ra                     |        | X      |        |        |
| IL2                       |        | X      |        |        |
| IL4                       |        | X      |        |        |
| IL6                       |        | X      |        |        |
| IL8                       |        | X      |        |        |
| MCP1                      |        | X      |        |        |
| MIP1a                     |        | X      |        |        |
| MIP1b                     |        | X      |        |        |
| sCD40L                    |        | X      |        |        |
| sIL2Ra                    |        | X      |        |        |
| TNFa                      |        | X      |        |        |
| Adiponectin               |        |        | X      |        |
| FGF23                     |        |        |        | X      |
| Insulin                   |        |        |        | X      |
| Leptin                    |        |        |        | X      |
| Osteopontin**             |        |        |        | X      |
| Osteocalcin**             |        |        |        | X      |
| ** Assay under evaluation |        |        |        |        |

